### Sample size

According to our previous study, Nepean Dyspepsia Index (NDI) scores of FD patients decreased by 12.2 points after acupuncture and by 7.8 points after sham acupuncture [23]. In this study, we anticipated a reduction of NDI score by 12 points after acupuncture with the *deqi* sensation and a reduction by 8 points after acupuncture without the *deqi* sensation, and we anticipated a reduction by 4 points in the wait-list control due to regression to the mean effect. With *α* = 0.05, 1 − *β* = 0.8, and a standard deviation of 10, we needed at least 96 participants in total. Considering a dropout rate of 10%, a total of 105 participants will be included in this trial. According to the sample size of previous blood-oxygenation-level-dependent fMRI (BOLD-fMRI) studies, 20 subjects is the reasonable sample size with stable statistical effect [24, 25]. Considering the dropout rate and loss of data due to head motion during fMRI scans, 25 participants from each group will receive fMRI scans in this study.

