## Data analysis

### Clinical data analysis

The intention-to-treat analysis will be used for all allocated participants in the baseline. This study focuses on the lasting-effect of acupuncture, and the observed data will be used as the primary analysis and last observation-carried-forward (LOCF) analysis will be taken as a sensitivity analysis. Clinical outcome will be analyzed using SPSS 22.0 statistics software (IBM SPSS Statistics, IBM Corp, Somers, NY, USA). Data on Skewed distribution will be normalized. Means, standard deviations, and 95% confidence intervals (CIs) will be used to describe the continuous data.

The demographic and baseline characteristics among three groups will be compared using one-way analysis of variance (ANOVA). A *χ*^2^ test will be used for categorical variables. Due to the occurrence of self-healing tendency in FD, it is important to testify the existence of acupuncture effect. The clinical outcome NDI and SF-LDQ scores will be compared between the acupuncture group and the wait-list group among three time points by using the repeated measures ANOVA (two independent groups with repeated measures). Then, the acupuncture group with and without *deqi* at three time points will be primarily compared using repeated measures model.

A two-sided test will be used during the analysis, with a significance level of 0.05. The data will be analyzed by statisticians who are blinded to the test settings.

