### The quality control program is the precondition for the result reliability

To improve the result reliability of this study, we design the quality control program from the following four aspects: (1) patient selection for the influence of age and handedness on cerebral function and structure have long been investigated, this study restricts the subjects to age between 18 to 45 years and being right-handed for baseline homogeneity; (2) sample size to obtain stable statistical power; we include 35 patients in each group for clinical evaluation and 25 patients in each group for the central mechanism study; and (3) fMRI scan; all scans are performed in the morning with the same scanner and operator. Scans on female participants are performed during the same menstrual cycle. Moreover, during the 24 h before scanning, participants will be asked to maintain their regular lifestyle and avoid overexertion and staying up late. No permission with alcohol, tobacco, tea, and coffee. Before being scanned, the emotional state of each participant will be evaluated via the emotional state assessment scales. To exclude significant emotional changes, during the scan participants will be asked to close their eyes and use a blindfold and to plug their ears with earplugs, stay awake, and not to speak. The scan room keeps the temperature between 18 and 22 °C, with humidity greater than 60% and noise less than 150 dB; (4) acupuncture manipulation; the acupuncture treatment will be performed by two experienced acupuncturists using a standard operation procedure. The *Deqi* sensation will be evaluated and recorded with the VAS after each acupuncture treatment.

In conclusion, the long-lasting effect is an important feature in acupuncture efficacy, and *deqi* may be one vital factor in producing the long-term effect. This study is the first functional brain imaging study which focuses on exploring the central mechanism of the long-lasting effect and the central influence of *deqi* on this effect with strict quality control. The results may provide a new approach to investigate the mechanism of the long-lasting effect.

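### The 80% power behind 96 participants belongs to the three-group overall test; the with-versus-without-deqi comparison has about 35%, and 105 falls slightly short of covering 10% dropout

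*Protocol article*

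**What the plan says.** The Sample size section anticipates NDI reductions of 12 points (acupuncture with deqi), 8 points (acupuncture without deqi) and 4 points (wait-list). It continues: "With *α* = 0.05, 1 − *β* = 0.8, and a standard deviation of 10, we needed at least 96 participants in total". The next step is "Considering a dropout rate of 10%, a total of 105 participants will be included in this trial". The discussion of quality control repeats the per-arm number as a guarantee of stable power: "we include 35 patients in each group for clinical evaluation".

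The Clinical data analysis section describes two comparisons by repeated-measures methods over three time points: acupuncture against wait-list, and then acupuncture with against without deqi. The word that marks priority is attached to the second. The section also states "A two-sided test will be used during the analysis, with a significance level of 0.05" and, on missing data, "the observed data will be used as the primary analysis", with last observation carried forward as a sensitivity analysis.

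**The concern.** Someone who reads the Sample size and Clinical data analysis sections together will take the 80% to apply to the comparison given priority, which is also the trial's scientific question: does deqi alter the lasting effect? The sample size text never says so and never says otherwise. If the 80% belongs to a different hypothesis, the trial may be far less able to detect a deqi effect than its readers believe, and a null result could be reported as evidence that deqi does not matter.

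The second question is narrower. The section gives a required number, a dropout rate and a final number, and the three should agree. Because observed data form the primary analysis, participants without outcome data do reduce the number analysed.

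**Working it through.** **Inputs.** From Sample size: mean reductions 12, 8 and 4; SD 10; α = 0.05; power 0.80; 96 required; 10% dropout; 105 included. From Study design: equal allocation, 35 per group. From Clinical data analysis: two-sided testing.

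**1. Reproducing the 96.** One-way ANOVA overall F test with equal arms of size n.
- Grand mean 8. Sum of squared deviations = 4² + 0² + 4² = 32.
- Effect size f = √(32/3)/10 = 0.327.
- Noncentrality λ = n × 32/100.
- n = 32 (N = 96): λ = 10.24, power 0.812.
- n = 31 (N = 93): λ = 9.92, power 0.798.

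So 32 per arm is the smallest equal-arm size that reaches 80%, and the stated 96 is recovered exactly.

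**2. Do pairwise readings give 96?** Normal approximation: n per arm = 2(1.960 + 0.842)² × SD²/δ².
- δ = 4 (with vs without deqi): 2 × 7.85 × 100/16 = 98.1, so 99 per arm (about 100 with the t distribution).
- δ = 8 (with deqi vs wait-list): 2 × 7.85 × 100/64 = 24.5, so 25 per arm, or 75 in three arms.

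Neither gives 32 per arm. Of the readings tried, only the overall test does.

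**3. Power for with versus without deqi.** Two-sample t test on change, δ = 4, SD 10, two-sided 0.05; noncentrality = 4/(10√(2/n)).

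| n per arm | noncentrality | power |
|---|---|---|
| 31.5 (105 less 10%) | 1.587 | 0.346 |
| 32 | 1.600 | 0.350 |
| 35 (no dropout) | 1.673 | 0.378 |

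The normal approximation gives about 0.36 at 32 and 0.39 at 35, which leads to the same conclusion.

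**4. The dropout step.**
- 105 × 0.90 = 94.5, that is 1.5 below 96.
- 96/0.90 = 106.7, so 107, or 108 for three equal arms.
- 96 × 1.10 = 105.6, so 106 if the total is rounded up.
- Loss that 105 absorbs: 1 − 96/105 = 8.6%, or 9 participants; 10% would be 10.5.

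**5. Overall-test power after 10% loss.**
- 94.5 evaluable (31.5 per arm): λ = 10.08, power 0.805.
- 94 evaluable: 0.798 if the extra participant is in the arm with the middle mean, 0.805 if in an outer arm.
- For comparison, 96 evaluable: 0.812.

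**The case against.** **On the deqi comparison.** The two-group t test is not the planned analysis. A repeated-measures model uses baseline and two later assessments and may be more precise. That is fair, and 35% should not be presented as the power of the planned model. But the article gives one SD and no correlation between time points, so nothing in it supports a higher figure. As a gauge of the gap: 80% power at 32 per arm needs a noncentrality of about 1.960 + 0.842 = 2.80, hence an effective SD of about 4/(2.80 × 0.25) = 5.7 in place of 10. It may also be said that this weakness has nothing to do with dropout. That is correct: with no loss at all, power is still only 38%.

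**On dropout.** A reader might infer from 94.5 against 96 that the trial misses its power target and must enrol 108. The documents do not support that. The target is 80%, and on the overall test the power after the stated 10% loss is still about 80%. There is also a plausible route to 105: 32 × 1.10 = 35.2 per arm, rounded to 35. The article gives no formula, so this is inference, but it would make the discrepancy a matter of rounding and convention. Finally, the Outcome assessments section says that data will be collected from participants who discontinue as well as those who complete, so stopping treatment does not by itself remove someone from the analysis. The full 1.5 deficit arises only if all the dropouts lack outcome data.

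**Conclusion.** The sample size statement needs correcting on two counts of very different weight.

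The main one is that the 80% is attached to no named test, reproduces as the three-group overall F test, and does not carry over to the comparison given priority in the analysis. For that comparison the plan's own 4 points and SD 10 imply about 35% power at 32 per arm and 38% at 35. This assumes a simple two-group comparison of change at a two-sided 0.05 level, with the stated SD applying to change in NDI. The repeated-measures model could alter it by an amount that the article does not allow one to calculate.

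The minor one is that 105 with 10% dropout yields about 94 to 95 evaluable participants, not 96. The gap is 2 to 3 randomised participants (105 against 107 or 108) and lowers overall-test power from 81.2% to about 80.5%. It is a slip in the text and does not show that the trial is too small for the overall test.

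**What to change.** Keep 105 and revise the Sample size section to say that:
- the 96 and its 80% power refer to the three-group overall test of NDI change;
- 105 with 10% dropout is expected to leave about 94 to 95 evaluable participants, with power of about 80% for that test (105 covers 8.6% loss before falling below 96);
- under the same assumptions, power for acupuncture with versus without deqi is about 35% in a simple two-group comparison, so a non-significant result there must not be read as showing that deqi has no effect.

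If the sponsor holds a correlation estimate that supports higher power under the repeated-measures model, it should be stated with the resulting figure. The cost is a few sentences of text. No additional participants are enrolled and neither the design nor the analysis changes. The Trial status section reports 61 participants recruited and recruitment still open, so the correction can be made before results are known.

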### Randomization

One hundred and five patients will be randomized into three groups by a third party using simple concealed randomization to avoid possible selection bias. With a computer-generated randomization digital table, patients will be informed using sealed envelopes whether they will receive acupuncture treatment and whether they will receive a fMRI scan. The allocation will be concealed to researchers, outcome assessors, and the statistician.

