## Methods and design

### Study design

This is a parallel-group, randomized controlled study. One hundred and five FD patients will be included and randomized with equal allocation to one of the three groups: acupuncture with *deqi* group, acupuncture without *deqi* group, and the wait-list group. Among 35 patients in each group, 25 participants will be selected randomly to undergo functional magnetic resonance imaging (fMRI) scans. This trial will include a 2-week baseline period, a 4-week treatment period, and a 4-week follow-up period. During the 4-week treatment, patients in two acupuncture groups will receive 20 sessions of treatments puncturing with or without *deqi*, while the wait-list group will not receive acupuncture treatment. Both the outcome assessments and fMRI scans will be performed at three time points including: the baseline, the end of the acupuncture treatments, and the end of follow-up (Figs. 1 and 2). This trial is reported in accordance with the Standard Protocol Items: Recommendations for Intervention Trials (SPIRIT) guidelines [22] (Fig. 2; Additional file 1).

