**Fig. 1 Fig1:**
[figure not shown]
Study schedule for data collection. The informed consent and examination will be conducted after recruitment. Matched functional dyspepsia (FD) patients will be then randomized into three groups, where two acupuncture groups will receive treatment. Both clinical outcomes and functional magnetic resonance imaging (fMRI) scans will be performed at three time points including: the baseline, the end of acupuncture treatments, and the end of follow-up. Adverse events will be recorded in the case report at any time during the study. a. *NDI* Nepean Dyspepsia Index, *LDQ* Leeds Dyspepsia Questionnaire, *SAS* Self-Rating Anxiety Scale, *SDS* Self-Rating Depression Scale, *BAI* Beck Anxiety Inventory, *BDI* Beck Depression Inventory, *VAS* Visual Analog Scale

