### Recruitment strategies

All patients will be recruited from outpatients and inpatients of the Digestive Department of the First Teaching Hospital of Chengdu University of Traditional Chinese Medicine (TCM) and the campus of Chengdu University of TCM between January 2016 to December 2018. Patients interested in this trial will be first evaluated by physicians. If they meet the criteria and decide to participate, they will be asked to sign the informed consent. Then, they will be included in this trial for randomization.

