### Patient safety

To provide health evaluation before randomization, physical examination for participants will be conducted including gastroscope examination, abdominal ultrasound, blood biochemical test (ALT, AST, BUN, serum creatinine), and electrocardiogram examination. To assess the risks associated with acupuncture, the blood biochemical test will be completed again at the end of treatment. Adverse events, such as pain, bleeding, fainting, or other severe events, should be processed immediately and recorded in the CRF carefully.

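### As written, the baseline scan and pre-scan mood rating appear to follow disclosure of acupuncture versus wait-list; the protocol should release scan status first and treatment only after baseline

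*Protocol article*

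**What the plan says.** The Randomization section states that "patients will be informed using sealed envelopes whether they will receive acupuncture treatment and whether they will receive a fMRI scan". The Study design section explains how the scanned subset arises: "Among 35 patients in each group, 25 participants will be selected randomly to undergo functional magnetic resonance imaging (fMRI) scans". The same section sets the timing: "Both the outcome assessments and fMRI scans will be performed at three time points including: the baseline", with further rounds at the end of treatment and the end of follow-up.

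On what comes before what:
- Recruitment strategies goes from eligibility and consent directly to allocation: "Then, they will be included in this trial for randomization".
- The Fig. 1 caption names consent and examination, and continues: "Matched functional dyspepsia (FD) patients will be then randomized into three groups, where two acupuncture groups will receive treatment". It describes the three assessment rounds after that.
- Patient safety is the only section that expressly puts a procedure ahead of allocation: "To provide health evaluation before randomization, physical examination for participants will be conducted". This is a health check and includes neither questionnaires nor imaging.
- The quality control section of the Discussion adds: "Before being scanned, the emotional state of each participant will be evaluated via the emotional state assessment scales".

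The Blinding section concedes that patients are hard to blind and gives the needling experience as the reason. Outcome assessors are blinded.

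**The concern.** A baseline should be measured before patients know what they will receive. This matters most when they report the outcomes themselves and are not blinded. Here the symptom, quality-of-life and mood measures are questionnaires. Blinded assessors do not protect such answers, because the patient supplies them.

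A patient told to wait through 4 weeks of treatment and 4 weeks of follow-up without acupuncture may rate mood or symptoms differently from one told to expect 20 sessions. Resting-state activity at the scan could differ too, and the quality control section itself treats emotional state as something to control before scanning.

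The Clinical data analysis section compares acupuncture with wait-list by repeated measures ANOVA over three time points, baseline being one of them, in order to establish that an acupuncture effect exists. A baseline difference produced by disclosure would enter that comparison wherever the baseline in question was taken after disclosure.

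**Working it through.** The question is one of sequence. The plan's own sample size figures (96, raised to 105) do not bear on it.

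**Step 1. Order of disclosure and baseline scan**
- Scan status is drawn within each allocated group (Study design), so it is fixed with or after allocation.
- Patients learn acupuncture yes/no and scan yes/no by the same route, described in one sentence (Randomization).
- A scan is due at baseline (Study design; fMRI scan). A selected patient has to know this before attending.
- If the two facts arrive together, the baseline scan follows disclosure of acupuncture versus wait-list. So does the mood rating given before it.
- Recruitment strategies, the Fig. 1 caption and Patient safety all fit this order. No readable section puts a baseline outcome before disclosure.

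**Step 2. How many patients**
- Scanned: 3 × 25 = 75. Share of the trial: 75/105 = 71%.
- All 105 complete the NDI, SF-LDQ, SAS, SDS, BAI and BDI at baseline. Nobody needs to know their scan status to do so, and the order relative to the envelopes is not stated.

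**Step 3. Which comparison**
- The sentence discloses acupuncture or no acupuncture, not deqi or no deqi. Wait-list patients would know their group. Patients in the two acupuncture groups would hold the same information as each other.
- Acupuncture versus wait-list is therefore exposed, and deqi versus no deqi is not shown to be.
- The part that follows most directly from the text (scan and pre-scan mood) touches any imaging comparison with the wait-list group. The planned NDI and SF-LDQ comparison with wait-list is touched only if those baselines also came after disclosure.

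**Step 4. How a shift would act**
- Let d0 be the difference between acupuncture and wait-list that disclosure causes at baseline, and d1 the part still present at a later visit. The comparison of changes moves by d1 − d0.
- If d1 = d0, the movement is zero. If d1 = 0, it equals d0 in size.
- The documents give no value for d0. As an illustration only, assume 1 to 2 NDI points, fully gone later. The planned differences from wait-list (Sample size) are 8 − 4 = 4 points without deqi and 12 − 4 = 8 points with deqi. The movement would be 1/4 to 2/4 = 25% to 50% of the first, and 1/8 to 2/8 = 12.5% to 25% of the second. With a persistent shift, both are 0%.

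**Step 5. Does opening the scan envelope first reveal the group?** In every group the chance of being scanned is 25/35 = 71%. Scan status alone therefore says nothing about treatment.

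**The case against.** The strongest reply is that the sequence is inferred. No section says when the envelopes are opened relative to the baseline scan, the questionnaires or the 2-week baseline period. The two schedule figures that might settle it are not available here, and the article condenses a fuller protocol. This stands, and it limits confidence. It does not remove the point, because the within-group draw and the joint disclosure are stated, and together they point one way.

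Three stronger readings are tempting, and the documents do not support them:
- A reader might infer a single envelope holding both facts. The text speaks of envelopes in the plural, and staged opening is compatible with it, although no staging is provided for.
- A reader might infer that all patients know their exact group at baseline, so that every clinical and imaging result is affected. The disclosure is of acupuncture versus none. The Clinical data analysis section gives the comparison with and without deqi as the primary one, and the fMRI data analysis section names only that contrast.
- A reader might take the reference to all allocated participants at baseline, in Clinical data analysis, as dating the questionnaires after allocation. That phrase defines the intention-to-treat set and dates nothing.

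It is also fair to object that any numerical size is assumed. The direction is not known either: wait-list disappointment that raised baseline symptoms and then faded would enlarge the wait-list improvement and work against acupuncture.

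**Conclusion.** The point holds in a limited form, with moderate confidence. On the plain reading, the baseline fMRI and pre-scan mood rating of 75 of 105 patients (71%) come after unblinded patients know acupuncture versus wait-list. For the NDI, SF-LDQ and the other baseline scales, the order is open.

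This can bias acupuncture versus wait-list. It is not shown to affect deqi versus no deqi. The size and direction of any shift are unknown, the percentages above only illustrate an assumed shift, and a shift that persisted equally would cancel.

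The conclusion rests on both facts being disclosed together and before the baseline scan. If disclosure is already staged, one sentence saying so resolves the matter. Otherwise this is an inexpensive improvement that removes an avoidable source of bias.

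**What to change.** In Randomization, have the third party place scan status and treatment allocation in separate sealed envelopes, both taken from the existing list. The order would then be:
1. Open the scan envelope after consent.
2. Complete all baseline questionnaires and, for those selected, the baseline scan.
3. Only then open the treatment envelope, just before the first session.

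State this order in Study design, Recruitment strategies and Outcome assessments. The randomization method need not change, because only the timing of disclosure moves.

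The cost is a second envelope set and a change of procedure partway through the trial. The Trial status section reports 61 recruited, so at most 105 − 61 = 44 patients would follow the new order. For those already enrolled, record the date of disclosure and the date of each baseline measure, and run a sensitivity analysis of acupuncture versus wait-list that takes account of which came first.
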